
### Participant timeline {13}

The following SPIRIT figure outlines the schedule of all study timepoints [19] (Fig. 2).

**Fig. 2 Fig2:**
[figure not shown]
The following SPIRIT figure outlines the schedule of enrolment, interventions, and assessments

### Sample size {14}

The sample size calculation is based on the primary endpoint “intraoperative blood loss during the parenchymal transection phase.” A difference of 100 ml in blood loss is considered clinically relevant, setting the non-inferiority margin at 100. Assuming no difference in mean blood loss between the two groups and using a standard deviation of 184 for blood loss in minimally invasive major liver resection [20], the initial single-center sample size required to achieve 80% power (*β* = 0.2) at *α* = 0.05 was calculated as 42 per group. Adjusting for a multicenter study design with an intra-class correlation coefficient (ICC) of 0.05 across four centers, the required sample size increases to 66 patients per group. Accounting for a 5% loss to follow-up, we plan to include a total of 132 patients across both study arms.

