### Trial design {8}

This study is a two-arm parallel-group, randomized non-inferiority trial in patients undergoing elective minimally invasive liver surgery with an allocation ratio of 1:1 per hospital and a follow-up period of 3 months. The flow diagram of the study is presented in Fig. 1.

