## Statistical methods

### Statistical methods for primary and secondary outcomes {20a}

The data will be managed and analyzed according to the applicable standard operating procedures (SOPs) within the shared unit of the clinical trial center. All relevant study information will be documented in case report forms (CRFs), which will be reviewed by the study team prior to data entry. A safety analysis will be conducted for all patients who underwent one of the interventions. Serious adverse events will be documented immediately, prompting notification of the principal investigator. Absolute and relative frequencies, as well as the severity and relationship to the intervention, will be compared between intervention groups.

The modified intention-to-treat (mITT) analysis will be used to evaluate the primary and secondary endpoints. The mITT set includes all randomized patients who initiated the intervention and met intraoperative inclusion criteria (e.g., exclusion of a PFO). Patients excluded intraoperatively due to contraindications (e.g., adhesions or peritoneal carcinomatosis) will not be included in the analysis.

The primary endpoint (intraoperative blood loss during the parenchymal transection phase) will be analyzed using linear regression if data follow a normal distribution. If normality is not met, a non-parametric bootstrap method will be employed to calculate confidence intervals. The 90% confidence interval (CI) for the mean difference between the two groups will be calculated, and the lower bound of this interval will be compared to the predefined non-inferiority margin of 100 ml to confirm non-inferiority. The corresponding *p* value will also be computed.

Secondary endpoints will also be analyzed:Continuous variables: These will be analyzed using descriptive statistics (mean, standard deviation, quartiles) along with two-sided 95% confidence intervals (CIs).Categorical variables: Absolute and relative frequencies will be reported, and two-sided *p* values will be calculated using the chi-squared test or Fisher’s exact test.

All statistical tests will be two-sided and conducted at a significance level of *α* = 0.05. Analyses will account for stratification to minimize bias and ensure accurate *p* values [22].

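### The sample size is raised from 42 to 66 per group for an ICC, although patients are randomised within centres and need no such inflation; the 5% loss is also placed where it adds nobody

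*Protocol article*

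**What the plan says.** The Sample size section of the protocol article gives these steps:

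- Margin: "setting the non-inferiority margin at 100" (ml).
- True difference: "Assuming no difference in mean blood loss between the two groups".
- Variability: "using a standard deviation of 184 for blood loss in minimally invasive major liver resection".
- Single-centre result: "80% power (*β* = 0.2) at *α* = 0.05 was calculated as 42 per group".
- Multicentre step: "intra-class correlation coefficient (ICC) of 0.05 across four centers, the required sample size increases to 66 patients per group".
- Loss step: "Accounting for a 5% loss to follow-up, we plan to include a total of 132 patients across both study arms".

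On the design, Trial design states an "allocation ratio of 1:1 per hospital". The allocation sections describe intraoperative randomisation of individual patients in 1:1 blocks, stratified by centre and by laparoscopic or robotic approach. The statistical methods section adds: "Analyses will account for stratification to minimize bias". It bases the non-inferiority conclusion on a 90% confidence interval, which corresponds to one-sided 0.05. The same section also describes all tests as two-sided at 0.05.

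**The concern.** There are two faults in one paragraph.

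First, the multicentre step treats centre as a cluster that carries a single treatment. In this trial every centre contributes patients to both arms in equal numbers. Whatever raises or lowers blood loss for everyone at a given hospital affects both arms alike and drops out of the comparison. A positive ICC of the outcome is then no reason to enlarge the trial.

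Second, the chain as printed does not run. If 66 per group is what is needed before losses, a 5% allowance must give more than 66. The plan gives exactly 2 × 66.

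What is at stake is the justification. The paragraph presents 66 as the number required, when on its own inputs 42 are. It also hides how much margin the planned cohort has over 80% power, and the sponsor needs that to judge the choice between one-sided 0.05 and 0.025. A reader who takes 66 as the pre-loss requirement would wrongly conclude that the trial is short.

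**Working it through.** **Inputs** (all from the Sample size section): margin 100 ml, true difference 0, SD 184 ml, power 80%, alpha 0.05, ICC 0.05, four centres, 5% loss.

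**1. Base figure.** n per group = 2 × (z₁₋α + z₁₋β)² × SD² / margin².

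- One-sided 0.05: 2 × (1.645 + 0.842)² × 184² / 100² = 41.9, so 42. This reproduces the plan and agrees with its 90% interval.
- One-sided 0.025: 2 × (1.960 + 0.842)² × 184² / 100² = 53.1, so 54.

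**2. How 66 arises.** The article prints neither a formula nor a cluster size. With the usual design effect 1 + (m − 1) × ICC, two routes lead to 66:

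- *Loss last:* m = 42/4 = 10.5; factor 1 + 9.5 × 0.05 = 1.475; 42 × 1.475 = 61.95, so 62; 62/0.95 = 65.3, so 66.
- *Loss first:* 42 × 1.05 = 44.1, about 44; m = 44/4 = 11; factor 1 + 10 × 0.05 = 1.5; 44 × 1.5 = 66.

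Rounding m up to 11 in the first route also ends at 66 (42 × 1.5 = 63; 63 × 1.05 = 66.15, about 66). In each case the 5% is already inside 66. To reach 66 from 42 without the loss, m would have to be about 12 (42 × 1.55 = 65.1, so 66), and four centres give no such m: 42/4 = 10.5, 66/4 = 16.5, 84/4 = 21, 132/4 = 33. Which route the sponsor took cannot be told from the article.

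**3. The loss step as printed.** 2 × 66 = 132, so nothing is added. Taken literally, 66 before loss would become 66/0.95 = 69.5, so 70 per group and 140 in total.

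**4. What the design needs.** Let each centre have its own level, shared by both arms. With 1:1 allocation inside the centre, the arm difference within that centre does not contain the level, and neither does the pooled difference. Its variance is 2 × SD²/n with no design effect. The requirement stays at 42 per group, or 42/0.95 = 44.2, so 45, with the 5% loss.

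**5. Power of the planned cohort.** After 5% loss, 66 × 0.95 = 62.7, so 62 to 63 evaluable. Power = Φ(100/SE − z₁₋α), with SE = 184 × √(2/n).

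| n per group | SE (ml) | one-sided 0.05 | one-sided 0.025 |
|---|---|---|---|
| 42 | 40.15 | 80.1% | 70.2% |
| 62 | 33.05 | 91.6% | 85.7% |
| 63 | 32.78 | 92.0% | 86.2% |
| 66 | 32.03 | 93.0% | 87.7% |

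**6. Simulation check.** Four centres, ICC 0.05 with 184 ml as total SD, individual 1:1 allocation within centre, one-sided 0.05, 10,000 runs per size. Power adjusted for centre (unadjusted in brackets) was 81.0% (80.5%) at 42 per group, 92.9% (92.4%) at 63 and 93.5% (93.0%) at 66. With the ICC present, 42 per group already reaches 80%.

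**The case against.** The strongest reply is that the slack is conditional and the inflation may be prudent. That stands in part. The power figures hold only for the stated inputs, and the article itself expects high pressure to reduce bleeding. Illustrative departures, all at one-sided 0.05:

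- A true difference of 20 ml against low pressure leaves 80 ml of margin: power 78% at 62 per group and 80% at 66.
- An SD of 230 ml: 79% at 63 per group.
- A treatment effect that varies between the four centres with an SD of 50 ml: SE = √(2 × 184²/63 + 50²/4) = √(1074.8 + 625) = 41.2 ml, power 78% at 63 per group.

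The last case is a real reason to inflate a multicentre trial. But an outcome ICC of 0.05 does not describe it, and the article states no such model.

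It is also fair that the article attaches 80% power to 42 per group, where it is correct, and that no patient or error rate is harmed by the excess.

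Some stronger readings are tempting, but the documents do not support them:

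- *The trial is 8 patients short (140 rather than 132).* This takes the printed order literally; the arithmetic indicates that the loss is already in 66.
- *The cluster formula should give 84 per group, from 21 patients per centre.* This corrects a formula that does not apply to this design.
- *The ICC lowers the requirement to 40 (41.9 × 0.95 = 39.8).* This needs 184 to be a total SD that includes variation between centres. The article takes it from a cited source that is not at hand and calls the resulting figure a single-centre one.
- *A 5% allowance is baseless because the endpoint is measured in theatre.* Consent may be withdrawn at any time, and the Confidentiality section foresees data destruction on withdrawal.

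**Conclusion.** The paragraph is wrong as written on two counts. The ICC inflation does not follow from a design that randomises individuals within centres, so the requirement on the stated inputs is 42 per group at one-sided 0.05, not 66. And 66 is labelled as the figure before loss when it must already include the loss for 132 to be right.

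The error is conservative. It is a fault of justification and reporting; neither an underpowered trial nor a wrong enrolment target follows from it. The size of the excess (power about 92% rather than 80%) rests on a true difference of 0, an SD of 184 ml and a common treatment effect across centres. It should be quoted with those conditions and not treated as guaranteed slack.

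**What to change.** Rewrite the Sample size paragraph:

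1. Remove the ICC inflation. State that 42 per group are required at one-sided 0.05 (54 if one-sided 0.025 is intended), and say which level applies.
2. State that 66 per group are randomised and that about 62 to 63 evaluable after 5% loss give about 92% power at one-sided 0.05 (about 86% at one-sided 0.025), assuming a true difference of 0, an SD of 184 ml and a common treatment effect across centres.
3. If the sponsor prefers to keep an inflation, name the model that justifies it, such as treatment effects that differ between centres, with its variance assumption. Show the sponsor's own chain of figures, and say that 66 already includes the 5% loss.

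The cost is one paragraph. The target of 132 patients, the randomisation and the analysis stay as they are.

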### Recruitment {15}

Recruitment of participants will be performed at the Heidelberg University Hospital, Ulm University Hospital, and the University Hospital Carl Gustav Carus Dresden, Germany, and at the Groeninge Hospital Kortrijk, Belgium.

## Assignment of interventions: allocation

### Sequence generation {16a}

The patients are intraoperatively randomized to either the control arm (low intra-abdominal pressure during parenchymal dissection) or the intervention arm (high intra-abdominal pressure), each in combination with deep neuromuscular blockade.

Prior to randomization, transesophageal echocardiography is performed to exclude a patent foramen ovale (PFO) or other structural cardiac defects associated with an increased risk of paradoxical gas embolism. Diagnostic laparoscopy is performed to rule out intra-abdominal adhesions, peritoneal carcinomatosis, or other contraindications to a minimally invasive approach or liver resection.

#### Stratification variables

Randomization is stratified according to the following variables:Center: to account for potential differences among participating clinicsSurgical procedure: conventional laparoscopic versus robot-assisted

### Concealment mechanism {16b}

Randomization is conducted as stratified block randomization with a 1:1 allocation ratio. Block sizes remain confidential until the end of recruitment. The REDCap Randomization Module Software is used to execute the randomization process. Allocation and assignment of participants will be conducted by members of the research team who do not have access to participants’ information other than the study identification code, the center, and the planned surgical procedure.

### Implementation {16c}

A qualified study physician or nurse will generate the allocation sequence, enroll participants, and assign them to interventions.

## Assignment of interventions: blinding

### Who will be blinded [21]

Due to the nature of the intervention, all staff members in the operating theater cannot be blinded. Therefore, blinding to group allocation will be limited. In both groups, the surgeons and assessors of outcomes are blinded to the study arm and intra-abdominal pressure. The anesthesiologists, who are responsible for the possible treatment of CO_2_ embolism, are not blinded to treatment allocation. The project coordinators, data managers, and the intervention coordinator will have access to group assignment but will not be involved in assessing participants in the clinical visits and follow-up. Baseline visit assessments will be conducted prior to randomization.

### Procedure for unblinding if needed [21]

Unblinding is allowed on the occasion of the occurrence of severe gas embolism.

## Data collection and management

### Plans for assessment and collection of outcomes {18a}

An outline of the study visits and a description of assessments are shown in Table 1.

**Table 1 Tab1:** Description of the time points and assessments of the study visits

Visit	Day	Description of assessments
Phase I: screening and inclusion in the study (intervention and control groups)		
V1	Outpatient clinic	- Inclusion/exclusion criteria - Informed consent - Assessment of sociodemographic data and medical history (*CRF 1*)
Phase II: intervention		
V2	Day of surgery	- Randomization to intervention/control group - Assessment of the surgical procedure (*CRF 2*) - Assessment of the anesthesia (*CRF 2*) - Collection of blood samples and peritoneal tissue samples at the beginning and the end of the parenchymal transection phase - Sampling of liver tissue from the liver resection specimen
Phase III: rehabilitation		
V3	POD 1	- Assessment of QoR-40 - Blood sampling
V4	POD 3	- Assessment of QoR-40 - Blood sampling
V5	POD 7	- Assessment of QoR-40
V6	Discharge from hospital	- Assessment of postoperative recovery (*CRF 3*)
Phase IV: follow-up		
V7	Follow-up at 3 months	- Telephone interview to assess outpatient rehabilitation (*CRF 4*)

### Plans to promote participant retention and complete follow-up {18b}

Participant retention is promoted by integrating the study follow-up into routine clinical care. Patients are often scheduled for a standard follow-up at 3 months following surgery. No additional visits are required; if an in-person follow-up is not feasible, a phone call will be conducted to ensure complete data collection.

### Data management {19}

The names of the patients/participants and all other confidential information are subject to medical confidentiality and the provisions of the General Data Protection Regulation (GDPR) as well as the relevant state or federal data protection laws (LDSG or BDSG). Data will be stored for a maximum of 10 years following the conclusion of the study. Only the principal investigator will possess the pseudonymization code, and the anonymization of personal data will be carried out in accordance with § 35 Abs. 2 LDSG BW once the data is integrated into the database. Disclosure of patient/participant data will only occur, if necessary, in a specific format. Third parties will not have access to original documents.

### Confidentiality {27}

Medical confidentiality and data protection regulations will be strictly observed. During the study, medical findings and personal information about the participants will be collected and recorded either in a personal file at the study site or electronically stored. Data relevant to the study will additionally be stored in a pseudonymized form. The study management will take all reasonable measures to protect the data in accordance with the European Union’s data protection standards. The data will be secured against unauthorized access, and decoding will occur only in case of withdrawal from the study and data destruction is required.

### Plans for collection, laboratory evaluation, and storage of biological specimens for genetic or molecular analysis in this trial {33}

As part of the PPULS study, biological specimens will be collected to evaluate the effects of different intra-abdominal pressures during surgery. During the procedure, two blood samples and two tissue biopsies (from the liver and peritoneum) will be collected to investigate the impact of varying pressures on tissue integrity. Following surgery, additional blood samples (approximately 15 ml per visit, totaling 45 ml) will be taken on days 1, 3, and 7 to monitor inflammatory markers and tissue damage. The collected specimens will be securely stored and used for molecular analysis within this study. After project termination, samples and data will be safely stored for 10 years and then disposed of. Their future use in ancillary studies is not yet planned.

## Statistical methods

### Statistical methods for primary and secondary outcomes {20a}

The data will be managed and analyzed according to the applicable standard operating procedures (SOPs) within the shared unit of the clinical trial center. All relevant study information will be documented in case report forms (CRFs), which will be reviewed by the study team prior to data entry. A safety analysis will be conducted for all patients who underwent one of the interventions. Serious adverse events will be documented immediately, prompting notification of the principal investigator. Absolute and relative frequencies, as well as the severity and relationship to the intervention, will be compared between intervention groups.

The modified intention-to-treat (mITT) analysis will be used to evaluate the primary and secondary endpoints. The mITT set includes all randomized patients who initiated the intervention and met intraoperative inclusion criteria (e.g., exclusion of a PFO). Patients excluded intraoperatively due to contraindications (e.g., adhesions or peritoneal carcinomatosis) will not be included in the analysis.

The primary endpoint (intraoperative blood loss during the parenchymal transection phase) will be analyzed using linear regression if data follow a normal distribution. If normality is not met, a non-parametric bootstrap method will be employed to calculate confidence intervals. The 90% confidence interval (CI) for the mean difference between the two groups will be calculated, and the lower bound of this interval will be compared to the predefined non-inferiority margin of 100 ml to confirm non-inferiority. The corresponding *p* value will also be computed.

Secondary endpoints will also be analyzed:Continuous variables: These will be analyzed using descriptive statistics (mean, standard deviation, quartiles) along with two-sided 95% confidence intervals (CIs).Categorical variables: Absolute and relative frequencies will be reported, and two-sided *p* values will be calculated using the chi-squared test or Fisher’s exact test.

All statistical tests will be two-sided and conducted at a significance level of *α* = 0.05. Analyses will account for stratification to minimize bias and ensure accurate *p* values [22].

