### Objectives {7}

The objective of this trial is to determine whether the maintenance of a low intraperitoneal insufflation pressure (IIP) of ≤10 mmHg during the parenchymal transection phase of conventional and robotic-assisted laparoscopic liver resections is non-inferior to a higher IIP of ≥14 mmHg in terms of intraoperative blood loss, gas embolisms, perioperative morbidity, and mortality.

The primary research question is as follows: Is the maintenance of a low IIP of ≤10 mmHg during the parenchymal transection phase of conventional or robotic-assisted laparoscopic liver resections non-inferior to a higher IIP of ≥14 mmHg in terms of intraoperative blood loss during the parenchymal transection phase?

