### Intervention description {11a}

Intraperitoneal insufflation pressures (IIP) during the parenchymal transection phase of liver resection will be different between the two study groups. Baseline IIP of the surgical procedure will be ≤10 mmHg. IIP will be elevated to ≥14 mmHg in the intervention group during the parenchymal transection phase of liver resection, while IIP will be maintained at ≤10 mmHg in the control group. Deep neuromuscular blockade will be applied in all patients and is defined as a train-of-four (TOF) of 0 or posttetanic count of 1–2. The quality of the surgical field is rated every 8 min on the Leiden Surgical Rating Scale (L-SRS) during the transection phase and every 15 min outside of it. When the field conditions reach inadequate scores of ≤3, IAP will be increased accordingly in steps of 2 mmHg.

Pringle maneuver, the clamping of the hepatoduodenal ligament, is obligatory and predefined as a sequence of 20 min of clamping followed by 5 min of perfusion.

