### Outcomes {12}

#### Primary outcome

The primary study endpoint is intraoperative blood loss in milliliters measured during the parenchymal transection phase. It will be referred to as *intraoperative blood loss during the parenchymal transection phase*.

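### The primary non-inferiority rule sets the lower confidence bound against 100 ml without fixing the contrast, the sign or the inequality, and it fails under every reading except one that the article does not state

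*Protocol article*

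**What the plan says.** **Endpoint.** "The primary study endpoint is intraoperative blood loss in milliliters measured during the parenchymal transection phase" (Primary outcome). A larger value is worse.

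**Hypothesis.** The research question in Objectives {7} begins "Is the maintenance of a low IIP of ≤10 mmHg during the parenchymal transection phase" and asks whether this is "non-inferior to a higher IIP of ≥14 mmHg in terms of intraoperative blood loss during the parenchymal transection phase". The abstract and the closing paragraph of the Discussion run the same way: LPP is tested and HPP is the reference.

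**Margin.** Sample size {14} reasons from a clinically relevant difference of 100 ml, "setting the non-inferiority margin at 100". No sign is given.

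**Decision rule.** Statistical methods {20a}: "The 90% confidence interval (CI) for the mean difference between the two groups will be calculated", after which "the lower bound of this interval will be compared to the predefined non-inferiority margin of 100 ml to confirm non-inferiority". No order of subtraction and no inequality are printed.

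**Arm labels.** Intervention description {11a}: "IIP will be elevated to ≥14 mmHg in the intervention group during the parenchymal transection phase of liver resection". Sequence generation {16a} likewise makes low pressure the control arm, with the alternative given as "or the intervention arm (high intra-abdominal pressure"). These labels run opposite to the hypothesis, in which low pressure is the arm on trial.

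**The concern.** A non-inferiority rule has to exclude the unfavourable end of the confidence interval. Which end that is depends on the order of subtraction and on whether high values are bad. Here high values are bad and LPP is the arm that has to prove itself, so the contrast that follows from the hypothesis is LPP minus HPP. Its unfavourable end is the upper bound, but the article names the lower one.

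Turning the contrast round makes the lower bound the relevant one, but the threshold is then -100 ml and the article prints 100 ml. The reversed labels make it harder to tell which contrast was meant: a programmer working from the hypothesis and one working from the arm labels would subtract in opposite directions.

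This is the only non-inferiority decision rule in the article. If it stays open until the data are in, the same interval can support opposite conclusions.

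**Working it through.** **Inputs.** Margin 100 ml, SD 184 ml, true difference 0, 80% power, alpha 0.05, 42 then 66 per group, ICC 0.05, four centers, 5% loss (Sample size {14}); 90% CI (Statistical methods {20a}).

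**1. Reproduce the plan's own figures.** For a one-sided 5% test:

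n = 2 × (1.645 + 0.842)² × 184² / 100² = 41.9, so 42 per group, as stated.

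A one-sided level of 2.5% would give 54. The plan therefore intends a one-sided 5% test, which agrees with a 90% interval. For the multicenter figure, the design effect 1 + (42/4 − 1) × 0.05 = 1.475 gives 42 × 1.475 = 61.95, so 62. Then 62/0.95 = 65.3, so 66, as stated.

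**2. Precision at 66 per group (normal approximation, no clustering).** SE = 184 × √(2/66) = 32.03 ml. Half-width of the 90% CI = 1.645 × 32.03 = 52.7 ml.

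**3. Probability of declaring LPP non-inferior.** Let d be the true excess loss with LPP. The lower bound of LPP minus HPP is normal with mean d − 52.7 and SD 32.03. The lower bound of HPP minus LPP has mean −d − 52.7 and the same SD. For example:

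- LPP minus HPP, lower < 100: Φ((100 + 52.7 − d)/32.03). At d = 100 this is Φ(1.645) = 0.95, and at d = 150 it is Φ(0.084) = 0.533.
- HPP minus LPP, lower > 100, at d = 0: 1 − Φ(152.7/32.03) = 1 − Φ(4.77), about 9 in 10 million.
- LPP minus HPP, lower > −100, at d = 100: Φ((100 − 52.7 + 100)/32.03) = Φ(4.60), above 0.999.
- HPP minus LPP, lower > −100, at d = 0: Φ((100 − 52.7)/32.03) = Φ(1.477) = 0.930.

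| Contrast | Success if | d = 0 | d = 100 | d = 150 | d = 200 |
|---|---|---|---|---|---|
| LPP − HPP | lower < 100 | >99.9% | 95.0% | 53.3% | 7.0% |
| LPP − HPP | lower > 100 | ~0 | 5.0% | 46.7% | 93.0% |
| LPP − HPP | lower > −100 | 93.0% | >99.9% | >99.9% | >99.9% |
| HPP − LPP | lower < 100 | >99.9% | >99.9% | >99.9% | >99.9% |
| HPP − LPP | lower > 100 | ~0 | ~0 | ~0 | ~0 |
| HPP − LPP | lower > −100 | 93.0% | 5.0% | 0.07% | ~0 |
| LPP − HPP | upper < 100 | 93.0% | 5.0% | 0.07% | ~0 |

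The last two rows are the same test and are the intended one. The first five are what the lower bound gives otherwise. In the fifth row, even an LPP arm that truly loses 100 ml less would succeed only 5% of the time.

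**4. Sensitivity.** The 95% at d = 100 is Φ(1.645) and depends on neither SD nor sample size. At 42 per group, the effective size if the design effect holds, SE is 40.2 ml. The first row then gives 65.5% at 150 ml and 19.9% at 200 ml, and the correct rule gives 80.1% at no difference and 5.0% at the margin.

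**The case against.** A reader might infer that the sentence cannot be rescued and that the trial will certainly reach the wrong verdict. The document does not support that. It prints no plus sign, and margins are often given as a magnitude whose sign follows from the contrast. By the article's own labels, intervention minus control is HPP minus LPP. For that contrast the lower bound is the right one, and with the margin at -100 ml the test is exactly the intended one (sixth row). The reversed labels are thus the one route by which the sentence could be correct. They also have a procedural explanation: baseline pressure is low in everyone, and only one group's pressure is raised for transection.

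It is also fair to say that the inequalities in the table are not printed in the article, so the error rates are conditional on them. A scenario with the upper bound below 100 ml for intervention minus control would answer the opposite question, but the article names the lower bound, so that scenario should not be attributed to it.

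A last defence is that a full protocol or analysis plan may give the signed inequality. That would excuse silence. Here, however, the article does state a rule, naming a bound and a margin, and that pair fails as printed. The valid reading needs two unstated assumptions, one of which takes the reference arm of the hypothesis as the intervention.

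**Conclusion.** The concern holds in this form: the primary decision rule is undetermined in direction and sign. It is wrong for LPP minus HPP, and wrong for a literal 100 ml in either order. It is valid only for HPP minus LPP against -100 ml, which the article does not say. A wrong conclusion is therefore possible but not established.

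Depending on the reading, the chance of declaring non-inferiority at a true excess of 100 ml runs from essentially zero to essentially 100%, against an intended 5%. At no difference it runs from about zero to above 99.9%, against 93.0% under the correct rule. These figures assume SD 184 ml, 66 per arm, normality and no clustering. Which readings are valid does not depend on those assumptions. Because the sentence governs the primary conclusion, it should be corrected before the data are analysed.

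**What to change.** In Statistical methods {20a}, replace the sentence with: *Difference = mean transection-phase blood loss in LPP minus HPP; LPP is non-inferior if the upper bound of the 90% CI is below 100 ml.*

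In Intervention description {11a} and Sequence generation {16a}, add that for the non-inferiority comparison LPP is the tested arm and HPP the reference, whatever the procedural labels.

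The cost is a wording amendment. The sample size calculation already matches this rule (42 per group reproduces), so no patients are added. The randomisation system and case report forms need no recoding, because the contrast is defined by pressure group and not by the words intervention and control.
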